### **53**    Eligibility of participants

Children must meet all of the inclusion criteria and none of the exclusion criteria to be eligible to participate in the trial.

### **54**    Inclusion criteria

Each subject being initiated on the study protocol must satisfy the following inclusion criteria at study entry:

- Healthy male or female child at least 24 months of age and less than 60 months of age at the time of study entry.
- Resident in the study area and with no plans to travel outside the study area during the period of subject participation.
- Informed consent for the study participation obtained from a parent (or guardian only if neither parent is alive or if guardianship has been legally transferred (see section 11.2).
- Willingness and capacity to comply with the study protocol as judged by a member of the clinical trial team.

### **55**    Exclusion criteria

No subject being initiated on the study protocol may have any of the following exclusion criteria at study entry:

- Serious, active, medical condition, including but not limited to:
  - chronic disease of any body system
  - severe protein-energy malnutrition (weight-for-height Z-score of less than -3)
  - known genetic disorders, such as Down's syndrome or other cytogenetic disorder
- Active wheezing
- History of documented hypersensitivity to eggs or other components of the vaccine (including gelatin, sorbitol, lactalbumin and chicken protein), or with life-threatening reactions to previous influenza vaccinations.
- History of documented hypersensitivity to macrolide antibiotics
- History of Guillain-Barré syndrome.
- Receipt of aspirin therapy or aspirin-containing therapy within the two weeks before planned study vaccination.
- Any suspected or confirmed congenital or acquired state of immune deficiency including but not limited to primary immunodeficiencies including thymus

disorders, HIV/AIDS, hematological or lymphoid malignancies (blood tests will not be routinely undertaken with this regard as part of the study).

- Any current immunosuppressive/immunomodulatory treatment or receipt of any such treatment within the six months preceding trial enrolment (for corticosteroids this is defined as a dose of prednisolone (or equivalent) of greater than 2mg/kg/day for one week or 1mg/kg/day for one month. The use of topical corticosteroids is not an exclusion criterion.
- The use of inhaled corticosteroids within the last one month.
- Receipt of an influenza vaccine within the past 12 months.
- Has any condition determined by investigator as likely to interfere with evaluation of the vaccine or be a significant potential health risk to the child or make it unlikely that the child would complete the study.
- Any significant signs or symptoms of an acute illness or infection including:
  - an axillary temperature of 38.0°C or above or documented fever of 38°C or above in the preceding 14 days.
  - Any acute respiratory infection within 14 days of enrollment visit.

If the reason for ineligibility is likely to be temporary (e.g. a fever of 38°C or above or acute respiratory infection) and either will or may resolve before the infant reaches 60 months, they will not be recorded as a screening failure but instead will be re-screened within an appropriate future time-window (e.g. at least 14 days after the last documented fever of 38°C or above or resolution of respiratory illness) and a decision made regarding eligibility at that point.

If eligibility is confirmed, subjects will be recorded in an enrollment log.

Those that are not eligible based on one or more exclusion factors will be noted as screening failures on the screening log, with reasons for exclusion documented.

## **56 The role of laboratory investigations in confirming eligibility**

No laboratory analysis will be routinely undertaken in the process of assessing a child's eligibility. Abnormal findings during history or examination may result in an infant being referred for further investigations or treatment outside the clinical trial itself according to local clinical practice. This would not, as a matter of course, preclude subsequent inclusion in the trial if an infant was confirmed to be eligible.

## **57 Withdrawal and discontinuation of subjects**

If after signing of the informed consent form, the investigator ascertains that the subject does not fulfill all criteria for study entry, the case report form (CRF) pages need not be completed. Only the reason for subject exclusion should be noted on the screening log. Data on screening failures will therefore be collected.

If a subject who does not fulfill all criteria for study entry is inadvertently deemed eligible and included in the trial (either randomized in the case of Groups A, B and C or given azithromycin in group D), the investigator must terminate the subject's participation in the trial. If the subject

was randomized and administered the study vaccine, the subject should be followed for safety for 21 days following administration of Nasovac-S, if possible. However, no further samples will be taken from the subject and the data will be excluded from the analysis.

A parent/guardian may withdraw a child from the study at any time without giving a reason. This will not in any way affect their care otherwise. A parent/guardian may either withdraw from further participation only (in which case all clinical samples and data obtained prior to withdrawal will be evaluated as part of the study) or withdraw from further participation *and* from the use of any clinical data/samples already collected. If the latter option is requested by the parent/guardian of the child, collected samples will be destroyed, a request made for data withdrawal and this process documented. Irrespectively, the clinical trial team will make all reasonable efforts to monitor, follow-up and when necessary treat adverse events under such circumstances according to the procedures outlined for this trial (see section 7).

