(Group D – vaccination and sampling schedule in Table 2), by administration of a single dose of oral azithromycin 28 days prior to receiving LAIV. This timeframe has been chosen based on pilot data from the the Gambia showing significant alternation in the nasopharyngeal microbiome approximately 1 month after single dose oral azithromycin in Gambian children aged 1 – 7 years in mass trachoma treatment campaigns ([name], unpublished, personal communication). These subjects will be matched as closely as possible by pre-antibiotic nasopharyngeal microbiome profile [1], age (24 – 35, 36 – 47, 48 – 59 months) and sex (in that hierarchical preference), in a nested case-control study, to n = 35 children recruited in the main clinical trial. This will be done after all children have been recruited and microbiome sequencing and analysis has been completed. To avoid allocation bias of these controls, an individual in the [name] laboratory blinded to the immunogenicity data will undertake this matching process. In brief, the microbiome profile matching will be performed by first categorizing which of eight described profiles each child's microbiome clusters with depending on the dominant taxa (e.g. *Staphylococcus*, *Streptococcus*, *Moraxella* etc.) as described previously by the [name] group [1].

The day 2 visit window for groups A, B and D is deliberately restrictive to allow both blood and NPS to be taken at a time when peak gene expression changes post-LAIV can be captured. The other visit windows are intentionally liberal to maximize the opportunity to obtain a full set of blood and NPS samples for the purpose of the analysis, whilst in each case, not compromising the scientific objectives they are designed to deliver. However, in each case, the intention will be to obtain the sample on or as close to the day specified as possible. The sampling schedule and associated laboratory assays to be performed on each clinical sample is detailed in Table 3. The procedure to deal with participants who default visit windows is discussed in section 5.4.

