## 22 Allocation concealment, randomization and blinding procedures

### 23 Allocation concealment and randomization

Following informed consent, subjects will be assigned a unique subject identification number (section 3.2.2) and details recorded on an enrollment log. If eligibility is confirmed according to the defined inclusion and exclusion criteria (section 5.3), children will be randomized into one of the three equally sized groups as defined in section 3.1 above (for groups A, B and C).

Randomization will be undertaken using pre-prepared, sealed opaque envelopes to maintain allocation concealment. Block randomization stratified by sex will be undertaken using a computer generated randomization sequence pre-prepared by an individual not otherwise involved in the study or its analysis. The block size and randomization sequence will not be known by any member of the investigator team, hence ensuring allocation bias is avoided. Information regarding the group into which a participant has been randomized will be revealed to the team only when opening the envelope.

At the time of randomization, the person undertaking randomization will take the next envelope in numerical sequence. The randomization list will be cross-checked by a second individual both of whom will be required to sign to document the process.

The 35 subjects for group D will be recruited sequentially after recruitment in groups A, B and C have been completed, during the 2nd recruitment season (January – June 2018).

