### **75 Final confirmation of eligibility and definition of enrolment**

Eligibility for enrolment will be confirmed on the basis of the above (Section 6.1.3). A child will only be defined as being enrolled in the trial once final confirmation of eligibility has been determined and randomization has occurred.

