**108 Time windows for the collection of adverse event data**

All adverse events that occur through day 21 post-vaccination with Nasovac-S in groups A, B and D will be assessed and recorded (during scheduled visits at day 2, 7 and 21 after vaccination or if subjects present to the clinical trial site due to illness in between these visits). All adverse events occurring through Day 28 following administration of azithromycin (Group

D only) will be assessed and recorded (at the scheduled visit at day 28 after azithromycin or if subjects present to the clinical trial site due to illness before this visit). Parents/guardians will be advised to contact the study team via telephone or attend the clinical trial site if their child is unwell in between scheduled study visits.

Group C will receive Nasovac-S after NPS has been taken on the day 21 visit, so they are also afforded the same potential benefit of influenza vaccination by participating in the study as groups A, B and D. Given the existing safety data on Nasovac-S (Section 4.1.9), no extra visits will be scheduled for group C specifically for the purpose of gathering adverse event data. Parents/guardians will, however, be advised to contact the study team or bring their child to the health centre if they have any concerns and adverse event data collected, graded and investigated as per AEs in other groups detailed in this section. This will be particularly relevant for post-vaccine AEs for 7 days following vaccination, but aligns with the agreement to assess all study subjects if they are unwell until October 31st of the year of vaccination.

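### The wrong-inclusion rule states no safety follow-up for children given azithromycin only, and its data exclusion does not spare the adverse event summaries

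*Combined protocol and SAP*

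**What the plan says.** Section 57 deals with children who fail the entry criteria but are included by mistake. It covers those "either randomized in the case of Groups A, B and C or given azithromycin in group D), the investigator must terminate" their participation. Follow-up is then set out for one case, a child who "was randomized and administered the study vaccine, the subject should be followed for safety for 21 days following administration of Nasovac-S, if possible". The paragraph closes: "However, no further samples will be taken from the subject and the data will be excluded from the analysis".

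Section 108 (Time windows for the collection of adverse event data) sets a wider duty for Group D. "All adverse events occurring through Day 28 following administration of azithromycin" are to be assessed and recorded, either at the scheduled visit 28 days after the drug or when the child presents ill. It sets a 21-day window after Nasovac-S for Groups A, B and D. Section 105 (Serious adverse event) has every SAE during the study reviewed and followed until it resolves or the child is stable. Section 115 (Safety reporting procedures) has SAEs sent to the sponsor and safety monitor within 24 hours. None of these three sections mentions eligibility.

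**The concern.** Two things look wrong in section 57.

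First, it brings azithromycin recipients into the termination rule but then attaches follow-up to vaccination. A Group D child whose ineligibility comes to light after azithromycin and before LAIV is terminated, and the section says nothing about what follows. One way this could happen is a missed exclusion such as "History of documented hypersensitivity to macrolide antibiotics", which bears directly on that drug.

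Second, it asks for 21 days of safety observation in ineligible vaccinees and then excludes their data, with no exception for safety.

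At stake is whether the adverse event summaries describe all children exposed to a study product or only those exposed and eligible. Several exclusion criteria (wheezing, hypersensitivity, immune deficiency, aspirin) mark children who may be at greater risk. Section 56 provides no routine laboratory testing for eligibility, so late discovery is possible. Where serious events are rare, leaving out one child can turn a summary count of one into zero.

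**Working it through.** The plan has no figure on this point to reproduce. The check sets the sections side by side and adds two simple counts.

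1. **Who is terminated.** Section 57: Groups A, B and C once randomised, and Group D once given azithromycin.

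2. **Who is given follow-up.** Section 57: a child both randomised and given the study vaccine. The window runs from Nasovac-S.

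3. **Is Group D randomised?** Section 23 says: "The 35 subjects for group D will be recruited sequentially after recruitment in groups A, B and C have been completed". Taken strictly, even a vaccinated Group D child falls outside the clause. But the protocol uses the word loosely. Section 75 says: "A child will only be defined as being enrolled in the trial once final confirmation of eligibility has been determined and randomization has occurred". Section 24 likewise gives Group D a suffix described as that of a randomised group. I therefore do not rest the point on this word.

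4. **The period before LAIV.** Section 21 describes Group D as defined "by administration of a single dose of oral azithromycin 28 days prior to receiving LAIV". Table 2 gives the Day 0 visit a window of +7 days. The interval is therefore 28 days, and up to 28 + 7 = 35 days. During it the child has had azithromycin and no vaccine, so the clause does not apply on either reading of the word in step 3.

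5. **Do other sections close the gap?**
   - Section 108 relies on the scheduled visit 28 days after azithromycin, or on the child presenting ill. In Table 2 that scheduled visit is the Day 0 LAIV visit. Section 57 does not say whether it survives termination.
   - Section 105 covers SAEs during the study, without saying whether a terminated child still counts.
   - The sentence in section 57 on continued monitoring and treatment of adverse events stands in the paragraph on withdrawal by a parent or guardian. It does not reach termination by the investigator for ineligibility.

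6. **How wide is the data exclusion?** Section 57 does not say which analysis it means. Section 58 shows that the protocol can set a narrow exclusion: it removes children given unplanned antibiotics only from the microbiome part of the primary objectives and keeps their samples for other objectives. Section 57 has no such limit. Safety summaries were also produced. Tables S10 and S11 compare adverse events between LAIV (n = 213) and control (n = 108) with P values.

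7. **Upper limit on the first gap.** Planned Group D is 35 of 365 children: 35/365 = 9.6%. This is the number who pass through the uncovered interval, not an estimate of how many are wrongly included. The documents give no rate of wrong inclusion, so no effect on adverse event rates can be calculated.

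**The case against.** A reader might infer that azithromycin-exposed children are dropped with no follow-up. The text does not support that. Section 57 does not restrict follow-up to vaccinees in so many words and does not forbid it in others. Sections 105, 108 and 115 record, follow and report events with no eligibility condition, and section 83 offers care at the trial site until 31 October. This part of the objection stands. What remains open is narrow: whether the scheduled enquiry 28 days after azithromycin still takes place after termination.

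It can also be said that the excluded data are only the sample-based results, because the sentence couples the exclusion with the end of sampling. In support, section 107 says there are no defined safety endpoints, and the planned analyses (sections 124 to 130) describe no safety population. That reading is possible, but nothing in section 57 states it, and comparative adverse event tables were in fact reported.

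A third argument is that serious harm would still surface. This is largely right. Individual SAE reporting under section 115 and the pause on any SUSAR under section 117 do not depend on membership of an analysis set. One wording difference is worth tidying: section 7.1.4 defines a SUSAR by relation to the study vaccine, while section 115 speaks of the study product. The summaries and the non-serious events are not protected in this way.

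Nor does the rule remove only vulnerable children. Wrong inclusion can also arise from age, residence or recent influenza vaccination, and the example of an eligibility deviation in section 135 is age calculated from date of birth.

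**Conclusion.** The point holds as a drafting defect in two parts. Section 57 is silent on children who received azithromycin but not yet LAIV, and it is not reconciled with sections 105 and 108. Its exclusion of data has no limit, so if followed literally it would take ineligible vaccinees out of the adverse event summaries, after asking for their safety to be observed. The second part is the stronger, because it concerns a stated rule rather than a silence. It rests on reading the undefined reference to the analysis as covering safety summaries, which the text allows but does not compel.

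The size is probably small and cannot be estimated from the documents. Zero-event confidence bounds do not measure it. With the one-sided 95% bound 1 − 0.05^(1/n), taking 7 children out of 220 (an assumed 3%) moves the bound from 1.35% to 1.40%, and taking 1 out of 35 moves it from 8.2% to 8.4%. The concern is the loss of particular exposed children from the tables, not a loss of precision.

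A reader might also take the LAIV denominator of 213 in Tables S10 and S11, against 220 planned for Groups A and B, as proof that ineligible children were removed. The documents do not say why the numbers differ. The tables have no azithromycin column, so they show nothing about Group D.

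**What to change.** 1. In section 57, limit the exclusion to the immunogenicity, transcriptomic and microbiome analyses. State that every child who received Nasovac-S or azithromycin stays in the adverse event and SAE summaries, and list wrongly included children separately.

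2. Reconcile section 57 with sections 105 and 108 for children who received azithromycin only, so that the protocol says one thing about their safety observation after termination. Which rule applies is for the sponsor and investigators to settle.

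The first change is a wording edit and needs no new visits or samples. Its downside is that the safety tables will contain a few ineligible children and may look slightly less favourable; the separate listing lets a reader see their contribution. The second is also a text change, and any further cost depends on how the sponsor resolves the sections.

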## **58 Missed visit windows and criteria for withdrawal**

Subjects that miss visit windows will continue on the study protocol and all procedures relevant to the *subsequent* visit undertaken as planned at the correct time. Samples for the missed visit window will *not* be collected. Samples that have already been collected will still be used for inclusion in analyses addressing relevant objectives.

In the event that subjects receive unplanned antibiotic therapy after commencing the study but prior to their planned final visit (i.e. the day 21 visit), the subjects will be excluded from analyses of primary objectives relating to nasopharyngeal microbiome changes. Samples collected will still be included in analyses relating to other objectives.

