**Table S10. Adverse events between baseline (day 0) and day 7 of the study**

| Adverse event | LAIV
(n=213) | Control
(n=108) | P value |
|----------------------|-------------------------|----------------------------|----------------|
| Fever                | 32 (15.0%)              | 11 (10.2%)                 | 0.23           |
| Sore throat          | 1 (0.5%)                | 0 (0.0%)                   | 0.48           |
| Chills               | 1 (0.5%)                | 0 (0.0%)                   | 0.48           |
| Muscle/joint pains   | 0 (0.0%)                | 0 (0.0%)                   | -              |
| Headache             | 4 (1.9%)                | 0 (0.0%)                   | 0.15           |
| Epistaxis            | 0 (0.0%)                | 0 (0.0%)                   | -              |
| Nasal congestion     | 7 (3.3%)                | 1 (0.9%)                   | 0.20           |
| Reduced appetite     | 9 (4.2%)                | 8 (7.4%)                   | 0.23           |
| Rhinorrhoea          | 103 (48.4%)             | 25 (23.5%)                 | <0.0001        |
| Rash                 | 6 (2.8%)                | 4 (3.7%)                   | 0.67           |
| Dyspnoea             | 1 (0.5%)                | 0 (0.0%)                   | 0.48           |
| Cough                | 54 (25.4%)              | 19 (17.6%)                 | 0.12           |
| Sputum production    | 5 (2.3%)                | 2 (1.9%)                   | 0.77           |
| Irritability         | 0 (0.0%)                | 1 (0.9%)                   | 0.16           |
| Vomiting             | 8 (3.8%)                | 5 (4.6%)                   | 0.71           |
| Lethargy             | 5 (2.3%)                | 1 (0.9%)                   | 0.37           |
| Diarrhoea            | 13 (6.1%)               | 12 (11.1%)                 | 0.11           |
| Ear pain             | 4 (1.9%)                | 0 (0.0%)                   | 0.15           |

Data are n (%). P values were derived from Chi-square test or Fisher's exact test where appropriate. LAIV=live attenuated influenza vaccine.

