## 13 Aims and Objectives

### 14 Study objectives

#### 15 Primary

- (i) To identify novel early systemic and mucosal molecular signatures following LAIV that are associated with subsequent robust nasal and oral influenza-specific immunoglobulin A (IgA) responses, in order to provide insight into the mechanisms of successful mucosal immunization.
- (ii) To identify associations between nasopharyngeal microbiota and nasal and oral influenza-specific IgA responses post-LAIV in Gambian children, to explore whether microbiome variability can explain suboptimal immune responses in some individuals to live intranasal mucosal vaccines in Sub-Saharan Africa.
- (iii) To establish whether LAIV impacts the nasopharyngeal microbiome, with a specific focus on the burden of *S. pneumoniae*.

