## 20 Study design

### 21 Type of study and design

All primary objectives and most exploratory objectives will be addressed through the conduct of a phase 4, randomized, controlled clinical vaccine trial. A total of 330 healthy children aged 24 – 59 months will be enrolled into one of three groups of equal size (3 x 110 children):

- (i) LAIV-vaccinated (Group A - blood sample at day 0, 2, 21)
- (ii) LAIV-vaccinated (Group B - blood sample at day 0, 7, 21)
- (iii) Control group (Group C)

Allocation concealment will be maintained from the start through the use of sealed envelopes. Block randomization stratified by sex will be used and a randomization sequence will be generated by an MRC Statistician not involved in the study. Investigators will not be blinded to group allocation from this point onwards as the sampling schedule differs between groups. Local laboratory staff will therefore not be blinded for this reason, but samples sent to external laboratories will be blinded (see section 3.2.3).

Two LAIV-vaccinated groups are included in order to achieve several exploratory objectives, which require blood sampling at different time points following vaccination, whilst minimizing the number of times children are bled times (i.e. 2nd blood sample at either day 3 or day 7 post-LAIV, but not both). The unvaccinated subjects will serve as a control group for the primary objective of assessing the impact of LAIV on the nasopharyngeal microbiome. Section 8 details the statistical considerations made to decide on the sample sizes to be recruited. The vaccination and sampling schedules for groups A, B and C are detailed in Tables 1.

Group C subjects will be administered LAIV after the NPS is taken on their day 21 visit, to offer them the same level of protection against influenza illness by participating in the study as those in groups A, B and D.

An additional 35 healthy children aged 24 – 59 months will be recruited in the 2nd phase of recruitment (Jan – June 2018) to assess the objective of how modulation of the nasopharyngeal microbiome with antibiotics impacts the mucosal immunogenicity to LAIV

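### Excluding the whole child for antibiotics started after randomisation can bias the LAIV–microbiome comparison and discards valid earlier swabs

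*Combined protocol and SAP*

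**What the plan says.** The rule is in section 58 (Missed visit windows and criteria for withdrawal). Its trigger is "In the event that subjects receive unplanned antibiotic therapy after commencing the study but prior to their planned final visit", which the text identifies as the day 21 visit. The consequence is that "the subjects will be excluded from analyses of primary objectives relating to nasopharyngeal microbiome changes", while "Samples collected will still be included in analyses relating to other objectives". It is worded alike for every group and makes no distinction by when the antibiotic was started. Group D's azithromycin is planned, and antibiotics before entry are not covered.

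The analysis affected is primary objective (iii): "To establish whether LAIV impacts the nasopharyngeal microbiome, with a specific focus on the burden of" *S. pneumoniae*. Section 128 (Impact of LAIV on the nasopharyngeal microbiome) analyses it as a comparison of vaccinated and unvaccinated children at days 7 and 21.

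Three other provisions treat similar situations differently:

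- After a missed visit window, section 58 says "Samples that have already been collected will still be used for inclusion in analyses addressing relevant objectives".
- When a parent withdraws a child from further participation only, section 57 keeps the samples and data already obtained.
- Antibiotics in the month before entry are handled in section 128 by adjustment, not exclusion.

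On blinding, section 21 says "Investigators will not be blinded to group allocation from this point onwards"; external laboratories are blinded. Table 1 gives groups A and B a day 2 visit that group C does not have.

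**The concern.** Randomisation protects the comparison only if the children analysed are the children randomised, or if those removed are removed for reasons unrelated to arm and outcome. Receiving an antibiotic happens after allocation, is decided in a field setting where arm is known, and is usually a response to illness. It may be related both to arm and to bacterial density, and where it is, the remaining children are no longer a randomised comparison.

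The second problem is separate and needs no assumption about arms. A child who starts an antibiotic on day 10 has day 0 and day 7 swabs that the drug cannot have affected, yet both leave the primary analysis. A future event decides whether an earlier, valid measurement counts.

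At stake is the plan's only randomised primary question: whether LAIV changes the microbiome and pneumococcal burden. Sections 124 to 130 describe no analysis that retains these children, so a reader of the results could not see whether the rule mattered.

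**Working it through.** **1. The plan's own figures.** Section 51 enrols 330 (110 per group, 220 given LAIV) and allows about 10% attrition. The required sizes are 200 given LAIV (section 122) and 100 per group: 200/0.90 = 222.2 and 100/0.90 = 111.1, against 220 and 110. The allowance reproduces to within rounding. It contains nothing separate for antibiotic exclusions.

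**2. Is this a power problem?** After 10% attrition, 198 LAIV children remain, or 99 per IgA-response group at 50% responders. Section 122 needs 82 per group for 80% power, and 1 − 82/99 = 17%. Even if the rule reaches objective (ii), which the wording leaves unclear, the size survives up to about 17% excluded. The issue is bias, not power.

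**3. Could antibiotic use differ by arm?** From Tables S10 and S11 (213 LAIV, 108 control; uncorrected chi-square):

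| Symptom | LAIV | Control | P |
|---|---|---|---|
| Rhinorrhoea, day 0–7 | 103 (48.4%) | 25 (23.1%) | 0.00001 |
| Rhinorrhoea, day 7–21 | 108 (50.7%) | 28 (25.9%) | 0.00002 |
| Cough, day 0–7 | 54 (25.4%) | 19 (17.6%) | 0.12 |
| Fever, day 0–7 | 32 (15.0%) | 11 (10.2%) | 0.23 |
| Diarrhoea, day 0–7 | 13 (6.1%) | 12 (11.1%) | 0.11 (as printed) |

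The printed P values for the first four rows reproduce. Table S10 prints 23.5% for 25/108, which is 23.1%. Only rhinorrhoea clearly differs. With the extra day 2 visit and unblinded staff, a link to arm is possible. No antibiotic counts are given, so it cannot be shown.

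**4. What would a difference do?** Let q be the share of an arm excluded and D the mean log10 density of excluded minus retained children. The retained mean differs from the full-arm mean by −qD, so the LAIV−control difference shifts by −(q_L·D_L − q_C·D_C). All inputs below are assumptions:

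- 10% v 5%, D = ±0.3 to ±1.0 in both arms: 0.05 × 0.3 = 0.015 to 0.05 × 1.0 = 0.05, sign opposite to D.
- 15% v 5%, same D: 0.10 × 0.3 = 0.03 to 0.10 × 1.0 = 0.10, sign opposite to D.
- LAIV rate lower than control: the same sizes with the sign reversed.
- 10% in both arms, D_L = 0.5, D_C = 0: −0.05. Equal rates alone do not give zero; D must be equal too.

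For scale, the 1.5-fold increase in section 123 is log10(1.5) = 0.176, so 0.015 to 0.10 is 9% to 57% of it. That benchmark is a rise from baseline in vaccinated children, not an arm difference.

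**5. How many valid swabs are lost?** Every child treated after day 0 has a clean baseline swab. If starts were uniform over days 1 to 21 (assumption), 14/21 = 67% of excluded children would also have a clean day 7 swab at nominal visit days. If the swab were taken at the end of its 7-day window (day 14), the share is 7/21 = 33%. At nominal days, dropping only post-antibiotic samples cuts the loss at day 7 from q to q/3: with q = 10% of 198 LAIV children, from about 20 to about 7.

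**6. Internal consistency.** Read literally, the rule removes these children from the pneumococcal density analysis (primary) but keeps them in the *S. aureus* density analysis (exploratory), although section 128 describes one regression approach for both.

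**The case against.** The rule is pre-specified and neutral on its face, and it has a scientific reason: an antibiotic disturbs the outcome being measured. Section 43 lists *S. pneumoniae* among azithromycin's targets, and section 21 cites pilot data of an altered microbiome about a month after one dose. Keeping every post-antibiotic sample in the primary analysis would answer a different question, the effect of LAIV whatever antibiotics followed. If LAIV children received more antibiotics, it could mask a rise in density. This stands, and it is why the fix below does not make an all-samples analysis primary.

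The objection also limits what can be claimed. A reader might infer that the rule biases the trial toward finding no rise in pneumococcal burden: more symptoms, so more antibiotics, so the LAIV children with the highest density are removed. The documents do not support that chain. Section 7.1.4 would attribute most solicited reactions in the first week, runny nose among them, to the vaccine, which could lower prescribing in LAIV children. Diarrhoea, reduced appetite and vomiting lean toward control in Table S10, none significantly. And density after an antibiotic may be lower, making D negative.

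A reader might also add the section 57 rule for children wrongly enrolled: "However, no further samples will be taken from the subject and the data will be excluded from the analysis". That is a separate matter, because the criteria concerned already apply at study entry.

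None of this defends discarding swabs taken before the antibiotic, or the absence of any analysis that retains these children.

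**Conclusion.** The point holds in two parts. With certainty: section 58 makes a whole-child exclusion on a post-randomisation event from a randomised primary comparison, it loses valid pre-antibiotic swabs, it is out of line with the plan's handling of missed visits and participation-only withdrawal, and no sensitivity analysis checks it. As a possibility: the exclusion can be related to arm, given unblinded staff, unequal visits and about twice the rhinorrhoea under LAIV.

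It should not be read as showing that the exclusion is arm-related, or that it favours a particular answer. The 0.015 to 0.10 log10 range rests wholly on assumed exclusion rates and density gaps, can take either sign, and is zero when both are equal across arms. It shows only that an effect large enough to matter against a 1.5-fold change is not ruled out. The change is worth making because it is cheap and its case does not depend on those assumptions.

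**What to change.** In section 58, with a matching sentence in section 128:

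- **Main analysis of objective (iii):** keep all randomised children and every sample taken before the first unplanned antibiotic dose; drop only samples taken after it. Use a repeated-measures model for days 0, 7 and 21 with arm-by-visit terms, so that children with incomplete series contribute.
- **Sensitivity analyses:** (a) all samples as randomised, whatever antibiotics were given; (b) the current whole-child exclusion.
- **Reporting:** tabulate antibiotic starts by arm and visit interval, with the number of samples dropped.
- **Scope:** say whether the rule applies to objective (ii), and align the pneumococcal and *S. aureus* density analyses.

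The cost is wording, one table and two further model runs. Section 114 already has concomitant medication documented; confirm that the start date is captured. The appendix's final density model already carries a participant random effect and study timepoint, so the structure is familiar. The downside is that dropping post-antibiotic samples still relies on a missing-data assumption: later densities must be predictable from arm, visit, covariates and the child's earlier swabs. Sensitivity analysis (a) probes that.
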